### Measurement of effect

#### Primary endpoint/translational endpoint

##### Immunological efficacy

Immunological efficacy will be assessed by quantifying circulating immune effectors that are specific for a selected panel of tumor antigens. This panel will include tumor antigens known to be expressed at high levels by over 80% of patients with melanoma or RCC and whose expression will confirmed in tumor biopsies taken before and after at least 2 cycles. Peptide libraries fully covering the sequences of tyrosinase, gp100 and Mart-1 for melanoma; 5 T4, CAIX/G250 and EGF-R for RCC; and survivin, MAGE-A3 and NY-ESO1 for both melanoma and RCC, will be utilized to stimulate peripheral blood mononuclear cells (PBMC) before and after therapy in IFN-g ELISPOT assays, according to the standard operating procedures currently used the our Somatic Cell Therapy Laboratory.

### Secondary endpoints

#### Predictive value of pretreatment serum biomarkers

Pretreatment concentrations of VEGF, fibronectin and of other relevant proinflammatory cytokines will be evaluated by SearchLight multiplex array analysis according to the manufacturer’s instructions (FDA-validated test). Serum sampling will be performed before each cycle to identify whether changes in marker values found during treatment can predict early therapy failure. The expression of CAIX in tumor tissue will be evaluated in pretreatment biopsies from RCC patients. In particular, both percentage and staining intensity will be recorded for each patient. In melanoma patients, tumor tissue removed before the start of treatment will be analyzed for the presence of N-Ras mutations.

#### Tumor assessment

This study will use ***immune-related response criteria (irRC)*** [45], a further refinement of mWHO criteria, to better document tumor response in subjects undergoing immunotherapy (Table 3). irRC were created because the natural history of clinical response observed in subjects treated with immunological agents, such as ipilimumab, differs from that observed in subjects receiving other classes of anti-cancer agents. The main differences between irRC criteria and traditional response criteria are as follows:

**Table 3 Tab3:** **Immune-related response criteria (irRC)**

**Index lesions**	**Non-index lesions**	**New measurable lesions**	**New non -measurable lesions**	**% Change in tumor burden**	**Overall irRC response**
CR	CR	No	No	−100%	irCR
PR	Any	Any	Any	≥ −50%	irPR
PR	Any	Any	Any	< −50% to < +25%	irSD
PR	Any	Any	Any	≥ +25%	irPD
SD	Any	Any	Any	< −50% to < +25%	irSD
SD	Any	Any	Any	≥ +25%	irPD
PD	Any	Any	Any	≥ +25%	irPD
SD	Any	Any	Any	< −50% to < +25%	irSD
SD	Any	Any	Any	≥ +25%	irPD
PD	Any	Any	Any	≥ +25%	irPD

*irRC*: Immune-related response criteria; *CR*: Complete response; *PR*: Partial response; *SD*: Stable disease; *PD*: Progressive disease.

measurable new lesions are incorporated into the tumor burden (*e.g.* added to the index lesions) and do not define progression unless the total measurable tumor burden increases by the required amount (25%).New non-measurable lesions (including bone lesions) are not considered progression if the total measurable tumor burden is stable or shrinking.Changes in non-measurable lesions contribute only in the definition of irCR.Progression of disease should be confirmed at two consecutive timepoints.

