#### Method and timing

Response will be calculated according to irRC criteria. For the purposes of this study, after baseline tumor staging performed on the day before the first treatment cycle, patients will be re-evaluated for response every 8 weeks during therapy and every 12 weeks during follow up. Confirmatory scans will also be performed no less than 4 weeks following initial documentation of objective response and before discontinuation of treatment due to irPD.

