### Secondary clinical efficacy endpoints based on irRC

***Immune-related major durable disease control rate (irMDDCR)***: the proportion of treated subjects showing a disease control of 24 weeks measured from week 12, or from the date of the first overall response of irCR or irPR, until the date of irPD or death (whichever occurs first). For a subject who undergoes tumor resection following disease control but prior to disease progression, duration of disease control will be censored at the date of the last evaluable tumor assessment on or prior to the date of resection. Any subject who is unevaluable for MDDC for various reasons, *e.g.* censoring, lost to follow up, not assessable or unknown tumor assessments, will be considered a non-responder.***Immune-related objective response rate (irORR)***: the proportion of treated subjects with an immune-related best overall response (irBOR) of confirmed irCR or confirmed irPR.***Immune-related time to response (irTTR)***: the time from first dosing date until the measurement criteria (using irRC) are first met for overall response of irPR or irCR (whichever status comes first, and provided it is subsequently confirmed).***Immune-related duration of response (irDOR)***: the time between the date on which the measurement criteria (using irRC) are first met for an irCR or irPR (whichever status comes first and provided it is subsequently confirmed) and the date of irPD or death (whichever comes first). For a subject who undergoes tumor resection following response but prior to disease progression, irDOR will be censored on the date of the last evaluable TA or prior to the date of resection.For subjects who are still alive and have no progressive disease, as assessed by the investigator using irRC, irDOR will be censored on the date of the last evaluable tumor assessment.***Immune-related progression-free survival (irPFS)***: the time between the first dosing date and the date of irPD, or date of death, whichever occurs first (*i.e.* subjects who die without reported irPD will be considered to have progressed on the date of death). For subjects with no reported post-baseline tumor assessment, irPFS will be censored on the day of first dosing. For a subject who undergoes tumor resection following disease control but prior to disease progression, irPFS will be censored on the date of the last evaluable tumor assessment or prior to the date of resection. For subjects who are still alive and have no irPD, irPFS will be censored on the date of the last evaluable tumor assessment.***Overall survival (OS)***: the time from randomization until the date of death. For those subjects who are still alive, OS will be censored at the recorded last date of subject contact, and for subjects with a missing recorded last date of contact, OS will be censored at the last date the subject was known to be alive.***Immune-related time to progression (irTTP)***: the time from randomization to the first date of documented irPD (or death). Subjects without progression will be censored at their last tumor assessment date. Subjects without progression but who receive additional follow-up anticancer therapy will be censored on the date of their last tumor assessment prior to receiving the new therapy. Subjects with progression following additional anticancer therapy will also be censored on the date of their last assessment prior to receiving the therapy.***Death on study***: any death occurring between the date of randomisation and up to 30 days after the end of treatment must be reported to the Coordinating Center within 24 hours as a serious adverse event (SAE), regardless of the relation to study drug(s). Deaths occurring during the study follow-up period (*i.e.* more than 30 days after the last vaccine dose) need only to be reported as an SAE if it is thought that there is a possible correlation with the study treatment(s). All deaths must be reported on the Death Report section of the CRF regardless of cause.

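### If irPD has to be confirmed, irTTP censors a patient who switches therapy before the confirming scan on the date of the scan that showed progression

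*Protocol article*

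**What the plan says.** All references are to the protocol article.

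- **Confirmation.** The irRC rules printed with Table 3 say "Progression of disease should be confirmed at two consecutive timepoints". The table itself assigns irPD from a single assessment showing an increase of at least 25%.
- **Scans** (Method and timing). Restaging takes place "every 8 weeks during therapy and every 12 weeks during follow up". A confirmatory scan is also planned "before discontinuation of treatment due to irPD".
- **irTTP** (Secondary clinical efficacy endpoints based on irRC). The event is "the first date of documented irPD (or death". A patient without progression who starts other anticancer therapy is censored at the last assessment before it. In addition, "Subjects with progression following additional anticancer therapy will also be censored on the date of their last assessment prior to receiving the therapy".
- **irPFS** (same section). Starting new therapy is not a reason for censoring. A death counts: "subjects who die without reported irPD will be considered to have progressed on the date of death". Otherwise, "For subjects who are still alive and have no irPD, irPFS will be censored on the date of the last evaluable tumor assessment".
- **irDOR** (same section). It ends at irPD or death and has no new-therapy rule.
- **irMDDCR** (same section). Patients who cannot be evaluated, including through censoring, count as failures.
- **Data.** The section on primary and secondary endpoints says that the time of progression and the start of other therapies are both recorded.

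**The concern.** Each rule is reasonable alone. The difficulty comes from combining the confirmation rule with the irTTP censoring rule. A patient whose tumor burden passes the threshold may start another drug before the second scan. If the first scan alone is not irPD, this patient has not progressed at the time of the switch, and anything seen afterwards is censored. The censoring date is the last assessment before the switch, which is the scan that showed the growth.

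The switch will often happen because of that growth, so the censoring is related to the outcome. Kaplan-Meier estimation assumes that censored patients have the same later risk as those who remain, and that would fail here. The irTTP curve would be too high. The trial plans only 19 patients, so a few such cases would move it visibly.

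**Working it through.** **1. No planned figure to reproduce on this point.** The article gives no progression rate, event target or switching rate. Its only design calculation is for the primary immune response: continue with at least 3 of 7, active with at least 11 of 19, at 40% against 70%. The sum over x = 3 to 7 of P(X1 = x) × P(X2 ≥ 11 − x) gives 0.0841 at 40% and 0.9028 at 70%. The stated errors of 0.10 are met. None of this depends on irPD.

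**2. One patient followed through the rules.** Suppose an increase of at least 25% is first seen at week 8, new therapy starts at week 10, and there is no scan in between.

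| Endpoint | First scan counts as irPD | Confirmation required |
|---|---|---|
| irTTP | Event at week 8 | Censored at week 8 |
| irPFS | Event at week 8 | Event at later confirmed irPD or death; if neither, censored at last evaluable assessment |
| irDOR (if a responder) | Ends at the first irPD scan | Ends at later confirmed irPD or death; if neither, censored at last evaluable assessment |

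The article does not say whether a confirmed irPD is dated at the first or the second scan. A confirming scan after the switch therefore does not settle the matter. For responses this is settled: irTTR and irDOR date a response from when the criteria are first met, provided it is later confirmed. There is no matching sentence for irPD.

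**3. Who can fall into the gap.** The confirmatory scan is tied to stopping treatment because of irPD. It does not reach patients who stopped IL-2 for toxicity or clinical deterioration. It also does not reach those who finished treatment and progress in follow-up, where the next scheduled scan is 12 weeks away. Patients who simply miss the confirmatory scan are also left over.

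**4. Effect at one time point (assumed counts).** Let k of 19 patients have a first irPD at week 8 and switch unconfirmed, with no other event by then.

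- Counted as events, the estimate just after week 8 is (19 − k)/19. For k = 2 it is 17/19 = 89.5%, and for k = 4 it is 15/19 = 78.9%.
- Censored at week 8, the estimate is 1 − 0/19 = 100%.
- The same 19 − k patients remain at risk afterwards in both versions, so later factors are identical and the ratio persists: 19/15 = 1.27 for k = 4 and 19/17 = 1.12 for k = 2.

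**5. Effect over follow-up (simulation, all inputs assumed).** There are 19 patients, exponential time to progression with median 16 weeks, and survival after progression with median 40 weeks. Scans are 8-weekly and follow-up is 96 weeks. Unconfirmed irPD is not counted, there are no scans after a switch, and a share s of patients with first irPD switch before confirmation.

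| s | Mean irTTP events | Mean irPFS events |
|---|---|---|
| 0% | 18.7 | 18.7 |
| 10% | 16.8 | 18.1 |
| 20% | 14.9 | 17.5 |
| 30% | 13.1 | 16.9 |
| 50% | 9.3 | 15.8 |

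The irTTP column can be checked directly: 19 × (1 − 2^(−96/16)) × (1 − s) = 18.7 × (1 − s), which agrees to within 0.1. At 20% switching, irTTP loses 18.7 − 14.9 = 3.8 events and irPFS loses 18.7 − 17.5 = 1.2. Most irPFS events are kept because deaths count, but they are dated later.

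**The case against.** The strongest reply is that the article never says an unconfirmed irPD is to be ignored. Table 3 assigns irPD from one assessment, and the irTTP event is the first documented irPD. Confirmation is written into irORR, irTTR and irDOR for responses but not into the irPFS or irTTP event. On that reading the first scan is the event, it precedes the new therapy, and neither censoring sentence applies. This stands as a possible reading. It does not remove the point, because the confirmation sentence is printed as part of the progression criteria. Two analysts could code the same patient differently.

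Second, the planned confirmatory scan covers patients who stop treatment because of irPD. This also stands, and it narrows the affected group to those in step 3.

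Third, such detail may belong in an analysis plan that is not shown. That would answer a complaint about silence. Here the article sets out its censoring rules, and the trouble lies in how they interact.

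A reader might infer more than the documents support:

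- **That the fastest progressors drop out of the event count.** No figure shows this. Early progressors who stop for irPD are the group covered by the confirmatory scan, and patients who die without switching count as events.
- **That irPFS loses events as irTTP does.** It has no new-therapy censoring, so the main effect is delay.
- **That irMDDCR is inflated.** Unevaluable patients already count as failures.
- **That early failures are hidden from the biomarker analysis.** The section on pretreatment serum biomarkers does not define early therapy failure through irPD, and progression and new-therapy dates are recorded separately.

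**Conclusion.** The point holds in a limited form and is conditional on one reading. If irPD counts only once confirmed, the irTTP rules censor unconfirmed switchers at the scan that showed progression, and irTTP is biased upward. irPFS and irDOR are affected mainly through later event dates. The primary endpoint, OS, irORR and irMDDCR are essentially unaffected, and no decision rule in the article rests on irTTP.

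The size is unknown because no switching rate is given. The overstatements of 10.5 and 21.1 percentage points at week 8 (100 − 89.5 and 100 − 78.9) assume 2 or 4 affected patients out of 19. They also assume no other event by then and that every first irPD is real progression, which is what the two-timepoint rule is there to question. The simulated counts likewise show direction and relative size, and are not a forecast. The texts allow two codings of the same patient and must be reconciled before analysis.

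**What to change.** Amend the irRC rules under Table 3 and the endpoint definitions, for analysis only:

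1. Date a confirmed irPD at the first scan that meets the threshold.
2. For irTTP, and consistently for irPFS and irDOR, count a first irPD followed by new anticancer therapy, clinical deterioration or death before any confirmatory scan as an event at that first scan.
3. Add a sensitivity analysis that requires confirmation and applies the present censoring rule.

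The two-timepoint rule still applies where a second scan is taken before any new therapy. irMDDCR needs no change.

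The cost is a few sentences. No extra scans are needed, and the progression and new-therapy dates are already to be recorded. Item 2 also needs clinical deterioration to be identifiable from the case report form, which is assumed here. The drawback is that an occasional pseudoprogression in a patient who switched early will count as an event; the sensitivity analysis shows how much depends on this.

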#### Radiologic assessment of tumor lesions

Contrast-enhanced CT scans of the brain, neck, chest, abdomen, pelvis and soft tissue (or MRI, if iodine contrast is medically contraindicated, *e.g.* for previous allergic reactions) will be performed for all patients during the Screening phase and at the time of tumor re-staging during the other study phases. CT scans of anatomic regions other than the chest, abdomen and pelvis must be performed in subjects in whom there is clinical suspicion of deep soft tissue metastases, *e.g.* lesions in the thigh.

Objective response or progression must be documented by the same imaging technique (CT scan or MRI) used during the Screening phase. The presence of progressive disease is not determined on the basis of only on a new lesion(s) found on bone scans. However, if bone lesions are identified at any time during the study, additional imaging studies of the lesion(s) must be performed to confirm the malignant nature of the new findings. Complete response must be confirmed by imaging studies showing the resolution of all metastatic lesions. Any subject who develops an objective tumor response (irCR or irPR) is required to undergo confirmatory scans no less than 4 weeks after the prior scan in order to verify the reliability of the radiologic finding.

#### Method and timing

Response will be calculated according to irRC criteria. For the purposes of this study, after baseline tumor staging performed on the day before the first treatment cycle, patients will be re-evaluated for response every 8 weeks during therapy and every 12 weeks during follow up. Confirmatory scans will also be performed no less than 4 weeks following initial documentation of objective response and before discontinuation of treatment due to irPD.

### Secondary clinical efficacy endpoints based on irRC

***Immune-related major durable disease control rate (irMDDCR)***: the proportion of treated subjects showing a disease control of 24 weeks measured from week 12, or from the date of the first overall response of irCR or irPR, until the date of irPD or death (whichever occurs first). For a subject who undergoes tumor resection following disease control but prior to disease progression, duration of disease control will be censored at the date of the last evaluable tumor assessment on or prior to the date of resection. Any subject who is unevaluable for MDDC for various reasons, *e.g.* censoring, lost to follow up, not assessable or unknown tumor assessments, will be considered a non-responder.***Immune-related objective response rate (irORR)***: the proportion of treated subjects with an immune-related best overall response (irBOR) of confirmed irCR or confirmed irPR.***Immune-related time to response (irTTR)***: the time from first dosing date until the measurement criteria (using irRC) are first met for overall response of irPR or irCR (whichever status comes first, and provided it is subsequently confirmed).***Immune-related duration of response (irDOR)***: the time between the date on which the measurement criteria (using irRC) are first met for an irCR or irPR (whichever status comes first and provided it is subsequently confirmed) and the date of irPD or death (whichever comes first). For a subject who undergoes tumor resection following response but prior to disease progression, irDOR will be censored on the date of the last evaluable TA or prior to the date of resection.For subjects who are still alive and have no progressive disease, as assessed by the investigator using irRC, irDOR will be censored on the date of the last evaluable tumor assessment.***Immune-related progression-free survival (irPFS)***: the time between the first dosing date and the date of irPD, or date of death, whichever occurs first (*i.e.* subjects who die without reported irPD will be considered to have progressed on the date of death). For subjects with no reported post-baseline tumor assessment, irPFS will be censored on the day of first dosing. For a subject who undergoes tumor resection following disease control but prior to disease progression, irPFS will be censored on the date of the last evaluable tumor assessment or prior to the date of resection. For subjects who are still alive and have no irPD, irPFS will be censored on the date of the last evaluable tumor assessment.***Overall survival (OS)***: the time from randomization until the date of death. For those subjects who are still alive, OS will be censored at the recorded last date of subject contact, and for subjects with a missing recorded last date of contact, OS will be censored at the last date the subject was known to be alive.***Immune-related time to progression (irTTP)***: the time from randomization to the first date of documented irPD (or death). Subjects without progression will be censored at their last tumor assessment date. Subjects without progression but who receive additional follow-up anticancer therapy will be censored on the date of their last tumor assessment prior to receiving the new therapy. Subjects with progression following additional anticancer therapy will also be censored on the date of their last assessment prior to receiving the therapy.***Death on study***: any death occurring between the date of randomisation and up to 30 days after the end of treatment must be reported to the Coordinating Center within 24 hours as a serious adverse event (SAE), regardless of the relation to study drug(s). Deaths occurring during the study follow-up period (*i.e.* more than 30 days after the last vaccine dose) need only to be reported as an SAE if it is thought that there is a possible correlation with the study treatment(s). All deaths must be reported on the Death Report section of the CRF regardless of cause.

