
### Statistical considerations

#### Study design/endpoints

Single center, open-label proof-of-principle phase II trial to assess immune response and biomarkers potentially predictive of response. The primary objective of this study will be ***immunological efficacy***, as assessed by quantification of circulating immune effectors specific for a selected panel of tumor antigens. Secondary endpoints will be the predictive value of pretreatment serum biomarkers in identifying patients who are likely to benefit from high-dose IL-2-based therapy, toxicity, response rate (RR) and overall survival (OS). The analysis will be performed on an intention-to-treat population, *i.e.* all patients who have received at least one cycle of therapy. All time-dependent clinical endpoints (RR and OS) will be estimated with the Kaplan-Meier method. Frequency tables will be performed for all categorical variables. Continuous variables will be presented using mean and standard deviation or median and range.

Given the explorative intent of the study and the limited sample size, we are aware of being exposed to a high level of false-positive results. Unless otherwise indicated, analysis of demography and baseline characteristics will be performed on all enrolled patients. Demographic and laboratory results will be summarized using descriptive statistics. The percentage of patients reporting an adverse event (AE) up to 30 days after the end of HD-IL-2 treatment will be calculated with 95% confidence intervals by type of AE. The overall rate of grade 3–4 related AEs will be calculated. In addition, summary statistics of clinically significant laboratory abnormalities will be tabulated. The time of disease progression and the initiation of new therapies will also be documented.

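### The irPFS rules conflict for a patient who dies before the first scan: an event at death, or censored on the day of first dosing

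*Protocol article*

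**What the plan says.** The irPFS entry in the protocol article (Secondary clinical efficacy endpoints based on irRC) contains four statements that bear on this point.

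- Definition: irPFS is "the time between the first dosing date and the date of irPD, or date of death, whichever occurs first".
- Death rule, as an explanatory clause to the definition: "subjects who die without reported irPD will be considered to have progressed on the date of death".
- No-assessment rule, in the next sentence: "For subjects with no reported post-baseline tumor assessment, irPFS will be censored on the day of first dosing".
- Closing rule: "For subjects who are still alive and have no irPD, irPFS will be censored on the date of the last evaluable tumor assessment".

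The scan schedule is in Method and timing: "patients will be re-evaluated for response every 8 weeks during therapy and every 12 weeks during follow up". The analysis population, in Study design/endpoints, is "all patients who have received at least one cycle of therapy".

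**The concern.** The first scheduled scan after baseline is at week 8. A patient who receives a cycle and dies before then has no post-baseline assessment and no documented irPD. The death rule makes this patient an event on the date of death, while the no-assessment rule censors the same patient at time zero. Nothing in the section says which prevails.

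The choice is not neutral. Early deaths are the worst outcomes, and under the no-assessment rule they are censored because the patient died too soon to be scanned. That is informative censoring in a trial of only 19 patients. The window also carries much of the treatment. With IL-2 every 3 weeks, cycles 1, 2 and 3 start on days 1, 22 and 43, and radiotherapy precedes cycles 1 and 3. So three of at most six IL-2 cycles and both radiotherapy courses are scheduled before the first scan. Deaths related to treatment in this period would be among those lost from irPFS.

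**Working it through.** **Reading the rules side by side**

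| Rule | Who it covers | Limited to living patients? | Result for a death before week 8 |
|---|---|---|---|
| Death rule | Dies without reported irPD | Not applicable | Event on date of death |
| No-assessment rule | No post-baseline assessment | No | Censored on day of first dosing |
| Closing rule | No irPD | Yes | Does not apply |

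The closing irPFS rule, the last irDOR rule and the OS rule are each limited to patients still alive. The no-assessment rule has no such limit. A patient with one cycle of treatment who dies before week 8 is in the analysis population and meets the first two rules.

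**Inputs**

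- N = 7 + 12 = 19 (Sample size/accrual rate).
- First scheduled scan at week 8 (Method and timing).
- Kaplan-Meier estimation. Study design/endpoints prescribes it for time-dependent clinical endpoints, naming RR and OS in brackets. Its use for irPFS is assumed here.
- k, the number of deaths before any post-baseline scan: not given in the document, so 1 to 4 is an assumed range.
- 7 patients event-free at 24 weeks: also assumed. The plan states no irPFS figure to reproduce.

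**Formula**

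Let m patients be event-free at a time t after week 8, with no other censoring before t. The Kaplan-Meier estimate then reduces to a proportion:

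- deaths as events: S(t) = m / 19
- deaths censored at time zero: S(t) = m / (19 − k)

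The ratio of the second to the first is 19 / (19 − k), whatever m is. Just before week 8, with no other early events, the estimates are (19 − k)/19 and 100%.

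**Results**

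| k | Just before week 8, deaths as events | Just before week 8, censored | 24 weeks, deaths as events | 24 weeks, censored | 19/(19 − k) |
|---|---|---|---|---|---|
| 1 | 18/19 = 94.7% | 100% | 7/19 = 36.8% | 7/18 = 38.9% | 1.056 |
| 2 | 17/19 = 89.5% | 100% | 7/19 = 36.8% | 7/17 = 41.2% | 1.118 |
| 3 | 16/19 = 84.2% | 100% | 7/19 = 36.8% | 7/16 = 43.8% | 1.188 |
| 4 | 15/19 = 78.9% | 100% | 7/19 = 36.8% | 7/15 = 46.7% | 1.267 |

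After the last of these deaths the shift is always upward. The median need not move. In a constructed set of 19 event times, most of them at scan dates, it stayed at 24 weeks under both rules for every k from 0 to 4. The distortion shows in the curve and in landmark rates.

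For scale, the standard error of 7/19 is √(0.368 × 0.632 / 19) = 0.111, or about 11 percentage points. The shifts at 24 weeks are about 2, 4, 7 and 10 points for k = 1, 2, 3 and 4.

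**The case against.** The best reply is that a coherent reading exists. Censoring rules ordinarily apply to patients without an event. The definition has already made death an event, so the no-assessment sentence can be taken to mean living or lost patients who were never scanned. Many analysts would read it that way. But the text does not say so. The sentence comes after the death rule and is the more specific of the two, and its neighbours carry the limit to living patients that it lacks. A programmer could follow it literally and be within the protocol.

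The remaining objections concern importance, and most of them stand.

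- irPFS drives no decision. It is absent from the secondary endpoints listed in Study design/endpoints and appears only among the irRC endpoints. The go/no-go rule uses immune response alone.
- Early deaths still count elsewhere. OS counts every death, irORR keeps treated patients in the denominator, and irMDDCR treats unevaluable patients as non-responders. This also means that the same early death would be a failure for irMDDCR and carry no information for irPFS.
- Eligibility requires a life expectancy above 3 months, which makes deaths before week 8 less likely. One such death shifts the 24-week figure by about 2 points, small beside the sampling error. The shift is nevertheless a bias in a known direction, and random error does not cancel it.
- If the analysis population means a completed cycle, a patient who dies during the first cycle is excluded before any censoring rule applies, and correcting the irPFS rule would not bring that patient back.

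It may also be said that an analysis plan could settle the matter. The protocol has not left the rule open, however; it states two rules that disagree.

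**Conclusion.** The point holds. As written, the irPFS entry gives two incompatible results for a treated patient who dies before any post-baseline scan. The censoring sentence, applied literally, inflates irPFS from the time of those deaths onward. The factor is 19/(19 − k) if all 19 patients are analysed and no one else is censored before the time of interest: 1.056 for one such death, 1.188 for three. In the illustration this is 36.8% against 38.9% to 43.8% at 24 weeks for one to three deaths. The number of early deaths and the 24-week rate are assumptions; with no such deaths there is no effect.

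The sample size, the two-stage decision on immune response and overall survival do not change. This is a correction that should be made, limited in weight because irPFS is a supporting endpoint. It is best made before outcomes are known: in an open-label, single-center trial, the choice of rule should not follow a look at who died early.

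**What to change.** Restrict the no-assessment rule and state the precedence. Suggested wording:

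*A patient without any tumor assessment after baseline who is not known to have died is censored at first dosing. A patient who dies with no documented irPD has an irPFS event on the date of death, whether or not any assessment was made after baseline.*

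This follows the protocol's own definition of irPFS. It needs one clause and no new data, since all deaths are already recorded on the case report form. No design figure changes. The only cost is that the irPFS estimate may be slightly less favorable if early deaths occur.
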